### Analysis

Outcomes will be compared at study completion at the patient, provider, and clinic levels. The analysis will be carried out on patient level variables using the generalized estimating equation approach to control for the effects of clustering. We will also adjust for the proportion of patients with guideline-concordant stroke prevention therapy at baseline and the other variables used in the minimization, as recommended by Taves [60]. Analysis will be performed on an intention-to-treat basis, and patient identifiers will be removed before transferring the data securely to analysts so that they will be blind to allocation. We will conduct the analysis as a longitudinal cohort design to permit exploration of patients whose treatments changed over time. As a sensitivity analysis, we will also conduct a repeated cross-sectional analysis to capture patients with newly developed AF during the intervention.

In keeping with similar trials in this literature, we considered a 10% difference in the primary outcome to be clinically important [48]. We assumed that 50% of patients with atrial fibrillation assigned to the usual care arm receive the primary outcome—using a control arm proportion of 50% is a conservative approach as it provides the largest sample size estimation. An EMRALD manual chart review of 7500 randomly selected adult patient charts discovered 192 patients with AF [16]; this 2.6% prevalence is similar to what has been reported in other primary care studies [79]. Based on that pilot data, we estimated that at least 100 patients would be available in each clinic (cluster). Therefore, using a reported intra-cluster correlation = 0.029 for warfarin uptake in patients with AF in primary care clinics [46], setting alpha = 0.05, and after adding 10% inflation for patient loss to follow up, 3276 patients (33 clinics) would be required to have 80% power [80].

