### Allocation

To avoid contamination, all physicians (and patients) belonging to a practice with shared administrative resources will be randomly assigned in a cluster to the intervention or control arm. The allocation will be done centrally based on clinic (clusters) by an analyst to ensure concealment from the study investigators. Restricted randomization has been recommended for cluster trials when baseline data is available [57]. We will use minimization [58] to evenly distribute clinics across trial arms and to improve balance across the following baseline covariates using the free software “MINIM” [59]: the total number of primary care physicians in each clinic, number of patients over 65 years, average age of all patients, rural location, average years of experience, average years on the EMR, number of patients with hypertension, number of patients with ischemic heart disease, number of patients with diabetes, number of patients with atrial fibrillation, number of patients with stage 3+ CKD, number of patients meeting blood pressure target (140/90 or 130/80 if patient has diabetes), number of patients 65 and older with atrial fibrillation or have a CHADS2 ≥ 1 and an anticoagulation prescription, and number of patients between 50 and 80 years of age with stage 3+ CKD on a statin unless contraindicated. Using baseline data from the participating clinics, continuous variables will be classified as high or low using the median value as the cut-point. Unlike stratification, increasing the number of covariates in minimization does not lead to increased risk for imbalance [60]. The participating practices will be minimized simultaneously at the initiation of the trial, reducing risk of selection bias.

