### Recruitment

All eligible physicians in EMRALD have consented to participate in the study. Although this intervention is multifaceted, it is designed to limit the amount of non-clinical time required by the physicians. The intervention is meant to facilitate physicians to provide the right treatment to the right patient by leveraging available data to use at the point of care. The toolkit can be discussed with physicians at a time that suits them. The pragmatic approach does not require them to participate in ways they do not think will be valuable. As the investigators do not intervene directly upon patients, no patient-level consent process is required. Patients are not directly recruited but are analyzed if they remain part of the participating physician’s roster throughout the trial.

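### The cohort analysis names only a clinic-level baseline proportion as its baseline-therapy covariate; adding each patient's own baseline anticoagulation status would give modest extra precision and guard against arm-specific roster loss

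*Protocol article*

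**What the plan says.** The Analysis section sets a patient-level model: "The analysis will be carried out on patient level variables using the generalized estimating equation approach to control for the effects of clustering". It then names the baseline covariate: "We will also adjust for the proportion of patients with guideline-concordant stroke prevention therapy at baseline", followed in the same sentence by the 'other' minimization variables. The word 'other' makes the baseline proportion one of the minimization variables. In the Allocation section the units being minimized are clinics, and the matching variable is a clinic count: "number of patients 65 and older with atrial fibrillation or have a CHADS2 ≥ 1 and an anticoagulation prescription". No covariate for an individual patient's baseline therapy is named.

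The same Analysis section defines the primary analysis as a cohort: "We will conduct the analysis as a longitudinal cohort design to permit exploration of patients whose treatments changed over time". The Recruitment section restricts who contributes an outcome: patients are "analyzed if they remain part of the participating" physician's roster for the whole trial. The sample size calculation allows 10% for patient loss.

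**The concern.** A patient's anticoagulant status at 12 months is likely to depend heavily on the same patient's status at baseline. The cohort design cannot follow changes in treatment without holding that baseline value, so the natural prognostic covariate is available but only its clinic average is named.

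Two things could be at stake. The first is precision, because a clinic average explains none of the variation between patients within a clinic. The second is protection against selection. Staying on the roster is determined after randomization. If the clinic proportion is computed over everyone present at baseline, it includes people with no outcome and cannot register who left. Should treated and untreated patients leave at different rates in one arm only, the analysed groups would differ in baseline therapy and the model would not correct for it.

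**Working it through.** **1. The plan's own sample size.** Inputs from the Analysis section: 50% v 60%, alpha 0.05 (two-sided assumed), 80% power, 100 patients per clinic, ICC 0.029, 10% inflation.

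- Per arm: (1.960 + 0.842)² × (0.25 + 0.24) / 0.10² = 384.6.
- Design effect: 1 + 99 × 0.029 = 3.871.
- Total: 2 × 384.6 × 3.871 × 1.10 = 3275.3, so 3276 as stated.

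This uses no covariate adjustment, so the point below does not alter it.

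**2. Where the variance lies.** The 34 clinics hold about 140,147 × 0.026 / 34 = 107 AF patients each, or 96 after 10% loss. Per clinic, the variance of the observed proportion is 0.25 × (0.029 + 0.971/96) = 0.25 × 0.0391. The between-clinic share is 0.029/0.0391 = 74%. A clinic-level covariate can therefore remove much of the variance on its own.

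**3. Precision.** The results below come from simulated trials: 34 clinics, mean 107 patients, ICC 0.029, 10% non-differential loss, no treatment effect, linear model, 1,500 runs per row. Persistence (percentage on therapy at 12 months if on / if off at baseline) and the variation in clinic size (CV) are assumptions; the article gives neither. Entries are the SE of the arm difference in percentage points.

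| Persistence | CV | Unadjusted | Clinic proportion | Patient status | Both |
|---|---|---|---|---|---|
| 85/15 | 0 | 2.86 | 1.67 | 1.61 | 1.62 |
| 85/15 | 0.8 | 3.30 | 1.91 | 1.83 | 1.85 |
| 75/30 | 0 | 2.39 | 1.92 | 1.88 | 1.91 |
| 75/30 | 0.8 | 2.76 | 2.15 | 2.08 | 2.14 |
| 95/15 | 0 | 3.08 | 1.56 | 1.47 | 1.49 |
| 95/15 | 0.8 | 3.64 | 1.75 | 1.67 | 1.70 |

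Replacing the clinic proportion with patient status lowers the SE by 2.1% (1.92 to 1.88) to 5.8% (1.56 to 1.47). Using both lowers it by 0.5% to 4.5%. A separate set of runs with about 95 patients per clinic gave roughly 1-8% for patient status against clinic proportion.

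Patient status alone is not always better. In a closed-form check with a patient-level correlation of 0.3 and a clinic-level correlation of 0.8, the SE was 2.50 points with the clinic mean and 2.81 with patient status alone. That is a reason to add patient status rather than swap it in.

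**4. Bias from arm-specific leaving.** Assume 50% on therapy at baseline, 10% loss in control whatever the baseline status, and persistence 88/15. Take the clinic proportion over all baseline patients. Then

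bias ≈ (treated share among intervention stayers − 0.50) × (0.88 − 0.15).

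- Intervention loss 8% treated / 12% untreated: share = 0.92/(0.92 + 0.88) = 0.511; bias = 0.0111 × 0.73 = 0.8 points.
- Loss 6% / 14%: share = 0.94/(0.94 + 0.86) = 0.522; bias = 0.0222 × 0.73 = 1.6 points.

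Simulation gave about 0.8 and 1.7 points, falling to about 0 and 0.1 with patient status in the model. In the runs of step 3, with untreated intervention patients leaving 5 points more often, the bias was about 0.6 to 1.1 points; at 10 points more often it was 1.2 to 2.3. With patient status it was about 0 throughout. If both arms lose patients in the same pattern, the two shares shift equally and the bias is 0.

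**5. Effect measure.** The article states no link function. Take 12-month control risks of 85% and 15% by baseline status, averaging 50%. A common conditional odds ratio of 2.16 gives 92.4% and 27.6%, averaging 60.0%. The marginal odds ratio is 1.5. Under a logit link, adding a strong patient covariate therefore changes the odds ratio being estimated, although the risk difference of 10 points is unchanged.

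**The case against.** The strongest reply is that the article never excludes patient-level status. It names no coding, link or covariate level, and a longitudinal GEE could carry baseline as a repeated measure. Detailed model specification is often left to an analysis plan, which is not shown. This stands in part: a reader might infer that the plan rules out the patient's own status, and the text does not say that. But the covariate is not simply left open. A proportion is named and grouped with clinic-level variables, so the written choice is the weaker adjustment.

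A reader might also infer that the primary estimate is biased whenever patients leave the roster. The article does not support that. Loss alone produced no material bias, nor did loss related to baseline therapy equally in both arms. The article gives only an overall 10% allowance and nothing on who leaves. Differential leaving is conceivable, because intervention clinics are prompted to list untreated patients for reassessment while control clinics are unaware of the AF study, but it is not documented. The article also does not say over whom the proportion is computed. Taken among stayers only, it removed the bias in simulation as well.

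Finally, one might infer that much precision is thrown away, or that the clinic covariate costs a scarce clinic-level degree of freedom. Neither carries weight. The clinic proportion already takes the SE from 2.86 to 1.67 points in the 85/15 case. One covariate more or less is minor when the Allocation section lists 14.

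**Conclusion.** The point holds as an inexpensive improvement to a stated choice, not as a demonstrated bias. Patient-level baseline status lowers the SE by roughly 1-8% relative to the clinic proportion, and by about 0.5-4.5% in the tabulated runs when both are kept. It also removes a bias of about 0.8 to 1.7 points, against a 10-point target, under the two loss patterns examined.

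The precision figures rest on assumed persistence and clinic variation. The bias figures rest further on loss that depends on baseline therapy differently by arm, and on a proportion taken over all baseline patients. The protection covers only leaving explained by baseline therapy, not by unmeasured factors.

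**What to change.** In the Analysis section, state that the primary GEE will include each patient's own baseline anticoagulation status (yes/no) as a patient-level covariate, and keep the minimization variables. State over which patients the clinic proportion is computed. Report the arm effect as a risk difference or another marginal (standardized) measure, so that a logit link does not change what is estimated.

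No new data collection is needed, since baseline therapy is already extracted from the EMR. The cost is a few sentences of wording and, if a logit link is used, a standardization step. The sample size is unaffected.

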At study commencement, 194 eligible physicians from 34 clinics with a total roster of 140,147 adult patients contributed data to EMRALD. These clinics are located across Ontario in urban, semi-urban, and rural settings. Comparisons conducted at ICES of the patient population of EMRALD physicians to the general primary care population in Ontario show that they are similar with respect to age and sex [56]. Participating physicians in EMRALD have access to the System for Audit and Feedback to Improve caRE (SAFIRE). SAFIRE is a secure, password-protected website used to provide performance feedback reports regarding quality of care for chronic disease. Data are available at both the aggregate and patient-specific levels. Prior to this trial, SAFIRE focused on comparing actual to guideline-recommended practice for patients with hypertension, diabetes, and/or ischemic heart disease. Physicians are able to compare their performance to other physicians that participate in EMRALD, and for physicians practicing in a group practice, physicians are able to compare their performance to other physicians within their own clinic, and their clinic performance compared to other clinics that participate in EMRALD.

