### Outcomes

The primary outcome is the proportion of patients with AF and an estimated yearly risk of stroke greater than 2% who are receiving stroke prevention therapy after one year. Specifically, the denominator will be patients aged ≥ 65 or who have a CHADS2 score ≥ 1. Offering such patients anticoagulation would be concordant with the 2014 CCS Guidelines [13]. Although the guidelines indicate that NOACs may be preferable over warfarin, we will group all anticoagulants together for the primary outcome because warfarin remains a suitable option for many patients. We acknowledge that anticoagulation may not be advisable in all these patients (e.g., high risk of bleeding, severe cognitive dysfunction making compliance unreliable, patient preference, etc.). However, it is impractical to accurately adjudicate appropriateness of withholding the anticoagulant using chart reviews alone given variability in charting practices and it is expected that the trial design will balance such patients across the study arms.

Secondary outcomes include the proportion of patients with the following characteristics: no CHADS2 risk factors and age <65 receiving anticoagulation; taking warfarin with at least six INRs measured per year; taking warfarin and time within a therapeutic range >60% using the Rosendaal method [73]; taking a NOAC with appropriate dosing (based on age and/or renal function); taking a NOAC but without renal function measured in 6 or 12 months; receiving other antiplatelets (e.g., aspirin alone, clopidogrel alone, aspirin plus dipyridamole, aspirin plus clopidogrel); taking an oral anticoagulant in combination with single or dual antiplatelet therapy; blood pressure (BP) and low-density lipoprotein (LDL) at target (to assess control of other stroke risk factors).

Process outcomes include the proportion of patients with AF in the cumulative patient profile, the proportion of patients with a formal stroke risk assessment completed, the proportion of patient charts with EMR-based tools used, and the proportion of providers who accessed the SAFIRE website to review their quality of care metrics.

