We developed a strategy for centralized identification of patients with AF in EMR data by performing a sensitive search for patients with a possible diagnosis of AF in the patient profile or with relevant treatments and/or results of cardiology tests that implicate a diagnosis of AF. An EMRALD team physician verified the charts to remove false positives from the study cohort, such as those with only brief runs of AF or those with only transient AF following surgery and follow-up testing that was normal. The methods for developing the search are similar to those used in previous studies [77] and based on previously described patient populations [16]. This search algorithm identified AF patients with one or more of the following components: (1) Recording of AF, including paroxysmal AF, “fibrillation”, and “flutter” in the problem list or history of past health fields of the EMR record [Additional file 3]; (2) electrocardiogram (ECG) and Holter monitor reporting AF; or (3) OAC prescription without clot, thrombosis, embolism, DVT, PE, valve replacement in the problem list, or history of past health fields, in combination with calcium channel blockers (CCB), ß-blockers, or digoxin prescription. The algorithm was able to accurately identify AF patients with a sensitivity of 78.6% (95% CI, 72.6–83.9%), a specificity of 99.9% (95% CI, 99.8–99.9%), positive predictive value of 95.1% (95% CI, 90.8–97.7%), and negative predictive value of 99.4% (95% CI, 99.1–99.5%). In addition, we developed and validated automated algorithms for identification of stroke and congestive heart failure to enable estimation of CHADS2 risk factors [78].

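### The 3276 patients and 80% power assume at least 100 patients in every clinic; the article's own figures make about 105 the average for all AF patients, and unequal clinic sizes are ignored

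*Protocol article*

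**What the plan says.** The sample size paragraph of the Analysis section rests on these inputs:

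- Control rate: "We assumed that 50% of patients with atrial fibrillation assigned to the usual care arm receive the primary outcome".
- Effect: "we considered a 10% difference in the primary outcome to be clinically important".
- Error rate: "setting alpha = 0.05" (sidedness not stated), with an intra-cluster correlation (ICC) of 0.029 and 10% inflation for loss.
- Cluster size: from a chart review that found 192 AF patients among 7500 adults, "we estimated that at least 100 patients would be available in each clinic (cluster").
- Result: "3276 patients (33 clinics) would be required to have 80% power".

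Three other sections bear on the cluster size. Participants reports that "194 eligible physicians from 34 clinics with a total roster of 140,147 adult patients contributed data to EMRALD". Measurement describes how AF patients are found: "The algorithm was able to accurately identify AF patients with a sensitivity of 78.6"% (95% CI 72.6 to 83.9%), with a physician removing false positives. Outcomes limits the primary analysis to AF patients with "an estimated yearly risk of stroke greater than 2% who are receiving stroke prevention therapy after one year", defined as age 65 or older or a CHADS2 score of 1 or more.

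The Allocation section lists physicians per clinic and AF patients per clinic among the minimization factors, and splits continuous factors into high and low at the median.

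**The concern.** A floor of 100 patients in every clinic is a strong claim when the whole pool averages little more than that. The paragraph also counts all AF patients found by manual chart review, whereas the trial analyses those whom an imperfect search finds and who also meet a risk rule. And it uses one cluster size for clinics that the plan itself treats as differing in size.

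The Abstract repeats that the study will be powered for a 10% difference. If the result is null, readers will take it as coming from a trial with 80% power for 10 points. The clinic pool is fixed and all eligible physicians have consented, so the trial cannot recruit its way out of a shortfall. The stated figure therefore has to describe the design that will actually be run.

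**Working it through.** **1. Reproducing 3276.** Two-sided alpha 0.05, 80% power, 0.50 versus 0.60, unpooled variance:

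- n per arm = (1.960 + 0.842)² × (0.25 + 0.24) / 0.10² = 7.849 × 49 = 384.6
- Design effect (DE) = 1 + (100 − 1) × 0.029 = 3.871
- Total = 2 × 384.6 × 3.871 = 2,978; × 1.1 = 3,275, or 32.8 clinics of 100, hence 33

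The figure is arithmetically right for a constant cluster size of 100.

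**2. Is 100 a floor?**

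- AF patients in the roster: 140,147 × 192/7500 = 3,588; / 34 = 105.5 per clinic
- Per physician: 3,588 / 194 = 18.5, so 100 AF patients need 100 / 18.5 = 5.4 average physicians
- Mean physicians per clinic: 194 / 34 = 5.7

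A mean of 105.5 is compatible with a minimum of 100 only if the clinics are nearly identical.

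**3. Can 3276 be reached?**

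- It needs 3,276 / 3,588 = 91% of all estimated AF patients to be both identified and in the denominator.
- At 78.6% sensitivity: 3,588 × 0.786 = 2,820, or 82.9 per clinic. At the upper confidence limit: 3,588 × 0.839 = 3,010.
- Keeping the false positives would not close the gap: 2,820 / 0.951 (the stated positive predictive value) = 2,965.
- Taking prevalence at its upper 95% limit, 0.0256 + 1.96 × √(0.0256 × 0.9744 / 7500) = 0.0292, gives about 4,088 AF patients; × 0.786 = 3,213. Only with both upper limits together (4,088 × 0.839 = 3,430) does the count pass 3276, and that is before the age/CHADS2 restriction.

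**4. Effect of a lower mean alone.** Equal clinics, 34 clinics, 10% loss, z method. The eligible share is not in the article, so 80% to 100% of identified patients is assumed:

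| Eligible share | Evaluable per clinic | DE | Needed, 2 × 384.6 × DE | Available | Power |
|---|---|---|---|---|---|
| 80% | 59.7 | 2.70 | 2,079 | 2,030 | 79.1% |
| 90% | 67 | 2.91 | 2,241 | 2,278 | 80.6% |
| 95% | 70.9 | 3.03 | 2,329 | 2,411 | 81.3% |
| 100% | 74.6 | 3.14 | 2,412 | 2,538 | 82.0% |

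The number needed falls with the cluster size, so power hardly moves.

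**5. Effect of unequal clinics.** At 82.9 × 0.9 × 0.9 ≈ 67 evaluable per clinic:

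- DE = 1 + ((1 + CV²) × 67 − 1) × 0.029
- Effective n per arm = 34 × 67 / (2 × DE)
- Power (z) = Φ(0.10 / √(0.49 / effective n) − 1.96)
- The t column uses a noncentral t with 34 − 2 = 32 df

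| CV (assumed) | DE | Effective n per arm | Power, z | Power, t | Detectable difference at 80% power, z / t (points) |
|---|---|---|---|---|---|
| 0 | 2.91 | 390.9 | 80.6% | 78.2% | 9.9 / 10.2 |
| 0.16 | 2.96 | 384.3 | 80.0% | 77.5% | 10.0 / 10.3 |
| 0.4 | 3.22 | 353.2 | 76.6% | 74.0% | 10.4 / 10.7 |
| 0.6 | 3.61 | 315.2 | 71.8% | 69.1% | 11.0 / 11.4 |

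To give the CV a scale: if half the clinics had 37 AF patients (two average physicians) and half had 174, the mean would be 105.5 and the CV (174 − 37) / 2 / 105.5 = 0.65. Even if every AF patient were found and eligible (95 evaluable per clinic after loss), power by z would drop below 80% at a CV of about 0.4.

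**The case against.** The strongest reply is that nothing is miscalculated. The 3276 reproduces, and it is a requirement conditional on 100 per clinic, not a fixed quota. That stands. A reader might set the 2,030 to 2,411 evaluable patients against the 2,978 required before inflation and infer a large deficit. The article does not support that: 2,978 belongs to a cluster size of 100, and at 67 per clinic the same formula needs 2,241 against 2,278 available.

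A reader might also infer that 34 clinics are needed because arms must be equal, leaving none spare. Nothing requires equal arms: 33 clinics split 17 and 16 would give 3,300.

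The power loss in step 5 depends on a CV and an eligible share that the article does not report, and on top of that on a t reference that an analysis plan may or may not adopt. This stands too. In addition, the Analysis section plans to adjust for baseline therapy and the minimization factors. If that removed 20% of the variance (an assumption), power with the t reference would be about 86% at CV 0, 83% at CV 0.4 and 78% at CV 0.6. The plan also calls its 50% control rate conservative.

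Finally, a condensed article may leave cluster-size variation to a fuller document. That would answer a complaint of omission. It does not answer a stated floor that disagrees with figures printed in the same article.

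**Conclusion.** The premise of at least 100 patients in each clinic is not supported by the article's own roster and prevalence, which make about 105 the mean of all AF patients and about 83 the mean of those the search would find. The stated 3276 is very unlikely to be reached from the 34 clinics.

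It is tempting to conclude that the trial has less than 80% power. The documents do not establish that. With equal clinics, power is about 79% to 82% by the plan's method, and baseline adjustment could raise it. What can be said is that the stated 80% is unsupported, mainly because clinic sizes are taken as equal while the allocation scheme treats them as varying. At 67 evaluable per clinic, a CV above about 0.16 takes power by z below 80%; CVs of 0.4 and 0.6 give about 77% and 72%, and a t reference takes off a further 2 to 3 points. These results assume 90% eligibility, 10% loss, the stated ICC of 0.029 and illustrative CVs. The point should be fixed, but it does not threaten the design.

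**What to change.** Treat the 34 clinics as fixed and report what they deliver:

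- Replace the floor of 100 per clinic and the 3276 patients in 33 clinics with the actual number of primary-denominator patients per clinic, their mean m and their CV, from the baseline extract already used for minimization.
- Restate power for 10 points, and the detectable difference at 80% power, using DE = 1 + ((1 + CV²) × m − 1) × ICC. State whether a z or t reference is used.
- Give both results unadjusted and adjusted for baseline therapy, with the variance reduction assumed for the adjusted one stated openly.
- Bring the power statement in the Abstract into line.

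The cost is a recalculation from data in hand and possibly a less favourable unadjusted figure. No patients, clinics or changes of design are needed.
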